## Abstract

**Background:**

The largest single cause of death among people with severe mental disorders is cardiovascular disease (CVD). The majority of people with schizophrenia and bipolar disorder smoke and many are also overweight, considerably increasing their risk of CVD. Treatment for smoking and other health risk behaviours is often not prioritized among people with severe mental disorders. This protocol describes a study in which we will assess the effectiveness of a healthy lifestyle intervention on smoking and CVD risk and associated health behaviours among people with severe mental disorders.

**Methods/Design:**

250 smokers with a severe mental disorder will be recruited. After completion of a baseline assessment and an initial face-to-face intervention session, participants will be randomly assigned to either a multi-component intervention for smoking cessation and CVD risk reduction or a telephone-based minimal intervention focusing on smoking cessation. Randomisation will be stratified by site (Newcastle, Sydney, Melbourne, Australia), Body Mass Index (BMI) category (normal, overweight, obese) and type of antipsychotic medication (typical, atypical). Participants will receive 8 weekly, 3 fortnightly and 6 monthly sessions delivered face to face (typically 1 hour) or by telephone (typically 10 minutes). Assessments will be conducted by research staff blind to treatment allocation at baseline, 15 weeks, and 12-, 18-, 24-, 30- and 36-months.

**Discussion:**

This study will provide comprehensive data on the effect of a healthy lifestyle intervention on smoking and CVD risk among people with severe mental disorders. If shown to be effective, this intervention can be disseminated to treating clinicians using the treatment manuals.

**Trial registration:**

Australian New Zealand Clinical Trials Registry (ANZCTR) identifier: ACTRN12609001039279

## Background

Cardiovascular disease (CVD) is the largest single cause of death among people with schizophrenia [1] and bipolar disorder [2]. The majority of people with schizophrenia and bipolar disorder smoke [3], considerably increasing their risk of CVD. Many also suffer from obesity, related to inactivity, unhealthy diets and some psychiatric medications [4]. Despite increasing recognition of the widespread impact that smoking and other unhealthy behaviours have on increased morbidity and mortality, treatment is often neglected among people with severe mental disorders. This randomised controlled trial of a Healthy Lifestyles intervention is the first of its kind to address these issues by employing a multi-component healthy lifestyle intervention for smoking and CVD risk behaviours among people with severe mental disorders.

The Healthy Lifestyles intervention was evaluated in a pilot program [5] which showed that setting a variety of goals, and assisting clients to make small steps towards these, can boost motivation and self-confidence to change unhealthy lifestyle behaviour. In that study we developed and piloted a multi-component Healthy Lifestyles intervention aimed at CVD risk reduction and smoking cessation among 43 smokers with severe mental disorders. Primary dependent variables were CVD risk score and smoking. Secondary dependent variables included weight, physical activity, unhealthy eating, substance use, psychiatric symptomatology, treatment retention, general functioning, and quality of life. Significant improvements in the primary dependent variables, CVD risk and smoking, and secondary dependent variables, weight and physical activity were found. There was also an improvement in diet although this did not reach statistical significance. The results of the pilot study suggested that the CVD risk factor intervention was feasible and effective in significantly reducing CVD risk and smoking among people with severe mental disorders. Excellent retention rates (84% completed all sessions), especially among males, attested to the importance and relevance of the intervention for people with psychosis. Participant reports indicated high levels of satisfaction with the program content, with access to nicotine replacement therapy (NRT) that was tailored to their needs, and with the opportunity to target a range of lifestyle factors that they considered important, but had hitherto been neglected. Many participants felt that they would have benefited from a longer intervention to provide scope to modify all the lifestyle issues targeted by the treatment and to consolidate gains. Other research [6] has reported that extended counselling can be significantly more effective than standard treatment, among depressed smokers. Consequently, we embarked upon the current larger-scale randomised controlled trial, with a longer treatment period; it is funded by competitive research grants from the National Health and Medical Research Council of Australia (project IDs 569210 and APP1009351). This trial is registered with the Australian New Zealand Clinical Trials Registry (ACTRN12609001039279).

## Methods/Design

### Study aims

The purpose of the research described here is to test the effectiveness of a multi-component intervention for smoking cessation and CVD risk reduction among people with severe mental disorders. It is hypothesised that the intervention will produce greater, more sustainable improvements in CVD risk and smoking status relative to the control condition at follow-up.

### Study design & setting

This is a prospective randomised controlled comparison study. Figure 1 shows the overall design. After completion of a baseline assessment and an initial face-to-face intervention session, participants will be randomly assigned to either a multi-component intervention for smoking cessation and CVD risk reduction or a telephone-based minimal intervention focusing on smoking cessation. Randomisation will be stratified by site (Newcastle, Sydney, Melbourne, Australia), Body Mass Index (BMI) category (normal, overweight: ≥ 25 and < 30; obese: ≥ 30) and type of antipsychotic medication (typical, atypical). A permuted block randomisation approach will be used so that the distribution of participants across treatment conditions will be maintained regardless of the final sample size. Following completion of the baseline assessment for each participant, the clinicians will be issued with a sealed randomisation envelope (by an independent person) which displays the participant identification code. The envelope will be opened by the participant at the conclusion of the initial session. This research will be conducted in three sites: Centre for Brain and Mental Health Research, University of Newcastle, New South Wales (NSW); School of Public Health, University of NSW, Sydney, NSW; and the Monash Alfred Psychiatry Research Centre (MAPrc), Monash University and The Alfred, Melbourne, Victoria, Australia. The researchers involved are experienced clinicians and scientists. Ethical approval was obtained for this study through the lead site of Hunter New England Human Ethics Committee and at each site.

**Figure 1 F1:**
[figure not shown]
**Study Design**.

### Patients

Approximately 250 smokers with a severe mental disorder will be identified from community mental health services, outpatient hospital clinics, psychology and general practices or using self-referral from the general community (e.g. via media advertisements). Written, informed consent will be obtained from each potential volunteer before baseline assessment.

### Inclusion Criteria

1) Age 18 years and over (minimum age level recommended for the use of nicotine replacement therapy, NRT);

2) Diagnosis of a severe mental disorder, as confirmed by the Mini International Neuropsychiatric Interview (MINI; [7]) - schizophrenia spectrum or bipolar disorder;

3) Current smoker (at least 15 cigarettes per day); and

4) Taking antipsychotic medication as prescribed for a period of at least two months, with intention to continue for the duration of the study.

### Exclusion Criteria

1) Non-English speakers;

2) Organic brain diseases; and

3) Medical conditions that would preclude treatment (NRT or overall, e.g. uncontrolled diabetes, pregnancy). Participants will be permitted to access additional treatments outside the proposed study, including psychiatric medication: any such treatments will be recorded at each assessment occasion. Any person who indicates suicidal ideation will be assessed using a standard suicide checklist. Only those persons judged as serious risk for suicide will have their participation suspended and be referred to the relevant psychiatric service. The same protocol will be used for people experiencing an acute phase of their psychotic disorder at any stage in the treatment program.

### Content of the Interventions

Treatment, including NRT, will be provided free to all participants across the face-to-face and phone-based conditions to assist with their attempts at tobacco abstinence and/or reduction. As stated above, all participants will receive an identical first session, after which they will receive four of the 24 weeks supply of NRT. The remaining NRT will be given to participants at weeks 4, 8 and 15. The NRT protocol is flexible and has been described elsewhere [8]. Briefly, participants smoking at least 30 cigarettes per day are eligible to receive double patching in addition to up to 12 × 2 mg lozenges per day, with NRT tapering occurring over the last month of delivery.

Therapists will be psychologists and both the active and control interventions will be guided by manuals (which are available upon request: [name], [name], [name], [name], [name], [name], [name], [name]: **Healthy Lifestyles intervention therapist manual **and **Healthy Lifestyles intervention telephone manual**. Unpublished manuscripts: University of Newcastle; 2010). Participants will be asked to provide details of their general practitioner (GP), psychiatrist and case worker and to consent to the therapist liaising with these professionals regarding assessment results and treatment progress, management of any acute episodes, and arranging follow-up.

The initial session before randomisation will be conducted face to face with the therapist and will focus on providing feedback to participants regarding their smoking (e.g. level of dependence) and other risk factors for CVD. A case formulation will be developed with the participant regarding their CVD status and unhealthy behaviours, with motivational interviewing (MI) being conducted to help the person consider changes in risk behaviours.

### Healthy Lifestyles Therapist Delivered Intervention (active treatment)

The active treatment protocol focuses on the adoption of more healthy lifestyle choices (see [8] for session by session summary). The initial session will be of 90 minutes duration, followed by seven one hour weekly sessions, three fortnightly hour long sessions and then monthly sessions of one hour duration for six months. A harm reduction focus is an important factor in the engagement and retention of participants, who may present with a range of preparedness to change the lifestyle factors currently impacting on their health and wellbeing. The intervention is designed to encourage smoking cessation and improvements in diet and physical activity, using a combination of MI and cognitive behaviour therapy (CBT) techniques. The initial focus of treatment will be based on the particular CVD risk factor(s), in addition to smoking, considered most problematic by the participant. Therapists will integrate messages and skill development about other CVD risk factors opportunistically. Self-help material will be provided throughout the treatment period, according to the CVD risk factors being discussed in each session.

#### Smoking cessation component

In addition to the provision of NRT that is common to both the Healthy Lifestyle therapist and phone-based conditions, the intervention includes education about the interaction between nicotine and symptomatology, medication and cognition, options for NRT, and examining beliefs regarding the relationship between smoking and symptoms. Despite a harm reduction focus, cessation as the ultimate goal will be encouraged for all participants, and a supportive follow-up telephone call will be made 2-3 days following the initial quit attempt [9]. Nicotine withdrawal symptom severity, cravings to smoke and adverse medication side-effects will be monitored each session.

#### Contingency reinforcement component

In the face-to-face condition, contingent reinforcement will be utilised, as it has been identified as an effective technique for facilitating smoking cessation amongst individuals with severe mental illness [10]. Expired carbon monoxide (CO) will be monitored each week, with positive reinforcement provided in the form of certificates and financial reimbursement (cash and vouchers) when participants meet predetermined criteria for success. The contingency reinforcement schedule will be based on a shaping model. Relative to an abstinent-only model, a shaping model rewards participants for successive reductions in CO readings as well as abstinence. This is in accordance with both abstinence and harm reduction approaches to substance use change. There are several components to this model. Firstly, session-by-session reimbursement is contingent upon demonstrated reductions in expired CO (explained in detail below). Secondly, participants receive a bonus once they meet the CO criterion for a given (set) number of consecutive weeks (e.g. three weeks in a row). Thirdly, an additional 'bonus' is on offer every week for participants who demonstrate abstinence (< 10 ppm expired CO). An advantage of this schedule is that it accounts for individual differences in baseline CO and rates of behaviour change. However, it is anticipated that many participants will be approaching and/or have met the abstinence criterion by the end of the weekly phase of treatment. As such, during the fortnightly and monthly sessions, reinforcement will be contingent upon abstinence only (<10 ppm expired CO). In summary, we will adopt a shaping schedule during the weekly phase of treatment whilst the fortnightly and monthly sessions will provide positive reinforcement only for abstinence.

#### Physical activity component

This component will be integrated with the other components of the Healthy Lifestyles intervention. Specific strategies will be introduced in session 4, with discussion of ways to increase levels of physical activity in everyday life (e.g. taking the stairs rather than the lift) and introduction of a graded walking program with provision of pedometers. Daily pedometer readings have been incorporated into participant monitoring forms, and will also be used to provide objective feedback to treating therapists about the extent of this activity in the day prior to each treatment session. Should participants express a desire to work on their physical activity earlier than session 4, then these strategies will be brought forward in the treatment sequence as required.

#### Dietary and nutrition component

This component will be integrated with the above Healthy Lifestyles strategies with an emphasis on increasing healthy food choices rather than on an 'ideal' caloric intake. Healthy eating habits will initially be discussed in session 7, with food planning and goal setting following in session 8. Specific motivational and CBT-related techniques will include encouraging participants to eat a variety of foods, eating foods that are high in fibre and low in fat, trying to eat five or more servings of fruits and vegetables a day and drinking plenty of water each day, eating regularly, and drinking alcohol within the recommended guidelines for Australia. Participants will be encouraged to consider issues that prevent them from making healthy choices (such as 'non-hungry eating', eating on a budget, cost effective meal plans and planning a shopping list). Finally, medication matters will be addressed, including drug-nutrient interactions and tips for dealing with medication side effects. As with physical activity, nutritional strategies will be brought forward to earlier sessions in the treatment program should participants wish to focus on these issues prior to session 7.

#### Booster sessions

Participants will receive six monthly booster sessions, during which a range of issues can be discussed. These sessions will include relapse prevention, overcoming lapses, review of previous sessions, methods to promote and maintain changes, and NRT tapering.

#### Monitoring

During each treatment session of the Healthy Lifestyle intervention, participants and therapists will complete the following range of formal measurements: side-effects from medication, nicotine withdrawal, weight, cigarettes per day, expired carbon monoxide (CO), NRT use over the past week, and average minutes walking continuously and briskly per week (based on physical activity diary entries).

### Phone-based Condition (control)

In order to orient participants to possible lifestyle changes and in particular, NRT use, those in the phone-based condition will receive an individual 90 minute face-to-face session a week following baseline assessment, as described above. To control for the number of therapist contacts, brief, manualised telephone calls (around 10 minutes) will be conducted with participants in this condition, to 'check in' about smoking and NRT use. Therapists will complete the following formal assessments for each phone session: adverse symptom checklist (antipsychotic medication), nicotine withdrawal and current symptoms of psychosis and mood. Self-report measurements of cigarettes per day, exercise and dietary intake will be taken each week during the phone-based sessions. These phone-based sessions will be made at the same intervals as therapist visits for the Healthy Lifestyles intervention condition (i.e. weekly for eight weeks, fortnightly for three sessions, followed by monthly calls for six months). In place of the phone-based sessions at weeks 4 and 8, participants will attend face to face sessions of 30 minutes duration where NRT is dispensed, and where any problems with NRT or symptomatology are monitored. Biomedical measures (expired CO and weight) will also be taken at these two sessions.

### Treatment Fidelity

Throughout the treatment period, all staff will receive regular weekly clinical supervision. Treatment fidelity will be monitored by delivering the therapy in a consistent fashion, closely adhering to the Healthy Lifestyles and phone-based (control) manuals. In addition, all treatment sessions will be audio recorded. An independent assessor will randomly select a 20% sample of tapes for each therapist, and rate tapes for treatment fidelity. Therapists will also be asked to bring along taped treatment sessions to clinical supervision sessions for discussion among the group.

### Outcome Measures

Outcome measures will be performed at baseline, during treatment (week 15), and at 12-, 18-, 24-, 30- and 36-months after baseline. Baseline assessments will be conducted prior to notification of randomisation status. Post-treatment and follow-up assessments will be conducted by independent assessors who will remain blind to intervention allocation.

All assessment instruments are widely used in mental health and/or tobacco treatment research and practice (see Table 1), and cover the domains hypothesised to be impacted upon by the treatment. CO measures will be taken one hour after arrival to partially control for effects of travelling in traffic, etc. Each participant will be offered up to $20AUD for each assessment, as reimbursement for their out of pocket expenses (e.g. travel).

**Table 1 T1:** Assessment instruments proposed for the current study

Instrument	Initial	15-wk	12-, 18-, 24-, 30- 36-months
*Tobacco Use*			
Opiate Treatment Index (OTI, quantity/frequency) [14]	√	√	√
Point Prevalence and Continuous Abstinence	√	√	√
Readiness to Quit Smoking [15]	√	-	-
Fagerstrom Test for Nicotine Dependence [16]	√	√	√
Expired Carbon Monoxide	√	√	√
Minnesota Nicotine Withdrawal Scale (MNWS-R)[17]	√	√	√
*Physical Activity*			
Readiness to change physical activity [18]	√	-	-
Physical activity screen (past week)	√	√	√
Average minutes walking per week	√	√	√
International Physical Activity Questionnaire [19]	√	√	√
*Dietary Habits*			
Readiness to change eating habits	√	-	-
24-hour recall of eating patterns	√	√	√
*Other CVD Risk Factors*			
OTI- alcohol and cannabis	√	√	√
Beck Depression Inventory - II [20]	√	√	√
Brief Symptom Inventory [21]	√	√	√
Body mass index (height, weight)	√	√	√
Waist-hip ratio (cms)	√	√	√
Auscultatory Blood pressure	√	√	√
Fingerprick Blood Tests (glucose, cholesterol, lipids)	√	√	√
*Treatment and Service Utilisation *[22]	√	√	√
*Diagnosis of psychosis and Symptom Measure*			
Brief Psychiatric Rating Scale [23]	√	√	√
Mini International Neuropsychiatric Interview [22]	√	-	-
*Functioning*			
Global Assessment of Functioning [24]	√	√	√
Medical Outcome Survey SF-36 [25]	√	√	√
Quality of Life Scale [26]	√	√	√
Impact of Weight on Quality of Life Questionnaire [27]	√	√	√
*Therapeutic Alliance & Intervention Satisfaction *[28]	-	√	-

As in the pilot study, the two primary outcome variables will be: (i) overall CVD risk index for participants; and (ii) smoking status; while the secondary dependent variables will include: weight; physical activity; unhealthy eating; substance use; psychiatric symptomatology; treatment retention and treatment alliance; service utilisation; general functioning; and quality of life. The CVD risk index calculation will be performed using the National Vascular Disease Prevention Alliance Absolute Risk Assessment [11] which is based on the Framingham algorithms [12]. Within this index, multiple risk factors of age, gender, systolic blood pressure, cigarette smoking, cholesterol and diabetes are used to predict CVD risk over 5 years [11]. Blood pressure measurements will be taken, as well as a small blood sample by finger prick to measure cholesterol and blood glucose levels. A general health and well-being questionnaire will also be completed by participants to identify lifestyle habits and previous medical history. Smoking status will be determined according to point prevalence abstinence (last 7 days) and continuous abstinence (since quit attempt), both of which will be biochemically validated by a CO reading of ≤10 ppm. Additionally, we will use 50% reduction in cigarettes per day as an indicator of smoking status [13].

We also plan to report the cost of delivering the intervention in real world settings and the cost impacts of the outcomes achieved by calibration of selected instruments used in the study (e.g. Quality of Life Scale, Global Assessment of Functioning) with those achieved in other costing studies.

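### A 50% cut in cigarettes per day, in effect self-reported by participants who know their arm, is an indicator of the primary smoking outcome without the CO check required for abstinence

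*Protocol article*

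**What the plan says.** Under Outcome Measures the protocol states that "the two primary outcome variables will be: (i) overall CVD risk index for participants; and (ii) smoking status". Smoking status is determined by 7-day point prevalence abstinence and by continuous abstinence since the quit attempt, "both of which will be biochemically validated by a CO reading of ≤10 ppm". The next sentence widens the outcome: "Additionally, we will use 50% reduction in cigarettes per day as an indicator of smoking status". It sets no CO condition, and reduction does not appear in the list of secondary variables.

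In Table 1 the tobacco quantity measure at each assessment is the "Opiate Treatment Index (OTI, quantity/frequency" instrument. The same table schedules expired CO at baseline, 15 weeks and every later visit, and the text describes how it is handled: "CO measures will be taken one hour after arrival to partially control for effects of travelling in traffic, etc".

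On blinding, "Post-treatment and follow-up assessments will be conducted by independent assessors who will remain blind to intervention allocation". Participants are not blind. Under Study design & setting, each participant opens the allocation envelope at the end of the first session. They then receive either hour-long therapist sessions or, for the most part, telephone calls of around 10 minutes.

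Contingent rewards are described for the face-to-face arm only. There, "session-by-session reimbursement is contingent upon demonstrated reductions in expired CO" during the weekly phase, and the later sessions reward CO-verified abstinence alone.

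**The concern.** The protocol applies two standards of evidence to one primary outcome. A claim of abstinence must be confirmed by a breath test. A claim of having halved consumption is taken as given, although the same breath test is done at the same visit.

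This matters because the number comes from a person who knows the allocation. Active-arm participants have had months of face-to-face encouragement to cut down, while control participants have had mainly short check-in calls. If that difference makes active-arm participants somewhat readier to report a large cut, the two arms will differ on this indicator with no difference in smoking. A blinded assessor records the biased answer faithfully. The strict p < 0.01 threshold in the Statistical Analysis section limits chance findings and does nothing against a systematic reporting difference. The result could then be presented as an effect on smoking status.

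**Working it through.** **Scope of the CO check.** In Outcome Measures the words "both of which will be biochemically validated by a CO reading of ≤10 ppm" refer back to the two abstinence definitions. The reduction sentence follows and stands outside them. On the text as written, one of three indicators of a primary outcome is unverified.

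**Is the reduction self-reported?** The Outcome Measures section does not use that term. The inference rests on the quantity/frequency instrument in Table 1, on the absence of any device or count for cigarettes, and on the control section, which says: "Self-report measurements of cigarettes per day, exercise and dietary intake will be taken each week during the phone-based sessions". The inference is sound, but it is an inference.

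**Size, as an illustration.** The documents give neither a reduction rate nor a misreporting rate, so there is no figure in the plan to reproduce for this indicator. Two inputs come from the plan:
- Retained sample: 250 × (1 − 0.18) = 205, which matches the Sample size calculation section and gives 102 per arm.
- Two-sided alpha 0.01, critical value 2.576. With no effect and no bias, the chance of significance in favour of the active arm is 0.5%.

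The rest is assumed: no true effect; the same true reduction rate p in both arms; a fraction f of active-arm non-reducers reporting a 50% cut; no over-reporting in control.

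The apparent active-arm rate is pA = p + (1 − p)f. For the two-proportion test, the probability of a significant result favouring the active arm is Φ[(pA − p − 2.576·se0)/se1]. Here se0 = √(2·p̄(1 − p̄)/102), with p̄ the mean of p and pA, and se1 = √([p(1 − p) + pA(1 − pA)]/102).

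| p | f | pA | se0 | se1 | argument of Φ | probability |
|---|---|---|---|---|---|---|
| 0.30 | 0.05 | 0.335 | 0.0652 | 0.0651 | (0.035 − 0.1679)/0.0651 = −2.04 | 2.1% |
| 0.30 | 0.10 | 0.370 | 0.0661 | 0.0659 | (0.070 − 0.1702)/0.0659 = −1.52 | 6.4% |
| 0.40 | 0.05 | 0.430 | 0.0690 | 0.0690 | (0.030 − 0.1777)/0.0690 = −2.14 | 1.6% |
| 0.40 | 0.10 | 0.460 | 0.0693 | 0.0692 | (0.060 − 0.1786)/0.0692 = −1.71 | 4.3% |

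The apparent differences are only 3 to 7 percentage points, yet the 0.5% becomes about 2-6%.

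**Sensitivity, same formula.**
- True rate 20%: 2.9% at f = 0.05 and 10.7% at f = 0.10.
- f = 0.15 with true rates of 30-40%: 9.9-15.6%.
- Dropouts counted as failures: with 125 per arm and both rates multiplied by 0.82, the results are 1.5-2.0% at f = 0.05 and 3.9-5.9% at f = 0.10.
- Control over-reporting at half the active rate: at f = 0.10 the compared rates are 0.335 v 0.370, or 0.430 v 0.460, and the result is 1.6-2.0%.
- Equal over-reporting in both arms: no difference arises and the figure stays at 0.5%.

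**The case against.** The strongest defence has four parts.

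*Payment and blinding.* A reader might infer that active-arm participants are paid to report fewer cigarettes, or that the whole trial is unblinded. The documents support neither. Rewards follow measured expired CO, so reporting fewer cigarettes earns nothing. Reduction is rewarded only in the weekly phase of eight weeks, before the 15-week assessment; after that only abstinence is rewarded. The payment described for attending assessments is up to $20AUD as reimbursement, offered to every participant. Outcome assessors are stated to be independent and blind. This part stands, and it leaves expectation and social desirability as the only route.

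*Size.* Zero over-reporting in control is the extreme case. Control participants have the identical first session, receive NRT, are asked about cigarettes at each call, and attend two face-to-face visits where CO is taken. This also stands: the figures above are conditional, and the sensitivity rows show how quickly they shrink.

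*Status of the indicator.* The sentence opens as an addition to the two validated measures, rests on a cited source, and suits the stated harm-reduction focus. The ranking of indicators may be set out in a fuller document. That is fair on ranking. It does not answer the point about scope, because the article itself says what the CO check covers and leaves this indicator out.

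*CO as a yardstick.* CO is a poor measure of partial reduction, so leaving it out is defensible. That is an argument for moving the indicator out of the primary outcome as much as for keeping it there unverified.

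**Conclusion.** The point holds in a limited form. One indicator of a primary outcome depends on reports from participants who know their arm and lacks the CO check applied to the other two, although the CO reading is taken at every assessment. Assessor blinding does not close this gap.

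The documents do not show that over-reporting is likely, how large it would be, or that it would differ between arms. The range of about 2-6% against a nominal 0.5% describes what modest one-sided over-reporting (5-10% of active-arm non-reducers, none in control) would do under no true effect, true rates of 30-40% and 102 per arm. It is not an estimate of this trial's error rate. The CO-validated abstinence indicators are not affected by this point. The change is worth making because it is cheap and the exposure falls on a primary outcome.

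**What to change.** In Outcome Measures, do one of the following before any outcome data are compared by arm:

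1. Name CO-validated abstinence as the primary smoking measure, and report the 50% reduction in cigarettes per day as a secondary or supportive outcome.
2. Keep the 50% reduction as an indicator, but count it only when accompanied by a pre-stated fall in expired CO from baseline at the same assessment.

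Either takes about one sentence and no new data, since CO is already scheduled at every visit. The first option gives the harm-reduction result less prominence. The second has a cost in sensitivity: CO is a coarse check on reduction, so some true reducers will go unconfirmed. Reporting the uncorroborated version alongside, labelled as such, would show how much depends on the check.
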